## Abstract

**Background:**

Total neoadjuvant therapy (TNT) is a novel treatment strategy that is an alternative to preoperative chemoradiotherapy (CRT) for locally advanced rectal cancer (LARC). However, an optimal protocol for TNT has not yet been established. The present study will be an open-label, single-arm, single-center trial to develop a new protocol.

**Methods:**

Thirty LARC patients at high risk of distant metastasis will receive CRT consisting of long-course radiation, concurrent with tegafur/uracil, oral leucovorin, irinotecan (TEGAFIRI), followed by mFOLFOX-6 or CAPOX before undergoing surgery.

**Discussion:**

Since previous findings showed a high percentage of grade 3–4 adverse events with the TEGAFIRI regimen for CRT and TNT, the primary outcome of this study will be safety and feasibility. Our regimen for CRT consists of the biweekly administration of irinotecan for good patient compliance. The novel combination approach of this treatment may improve the long-term outcomes of LARC.

**Trial Registration:**

Japan Registry of Clinical Trials jRCTs031210660.

**Supplementary Information:**

The online version contains supplementary material available at 10.1186/s12885-023-10941-z.

## Introduction

A new approach for locally advanced rectal cancer (LARC), such as Stage II/III lower rectal cancer, is preoperative chemoradiotherapy (CRT) followed by total mesorectal excision (TME) and adjuvant chemotherapy. Preoperative CRT has reduced local recurrence [1, 2] and improved long-term outcomes in patients who achieved pathological complete remission (pCR) [3]; however, distant relapse occurs in the majority of LARC patients receiving CRT [4]. Although adjuvant chemotherapy also plays an essential role in systemic recurrence in LARC patients receiving CRT [5], adherence to adjuvant chemotherapy with FOLOX and CAPOX is poor after surgery for a number of reasons, including postoperative complications, disease progression, and the toxic effects of pre- and postoperative treatments [2, 6]. Furthermore, in cases receiving long-course radiotherapy (RT), the interval between the diagnosis of LARC and systemic chemotherapy as postoperative treatment ranges between approximately four and six months. Systemic metastasis has been detected in this period in some cases. Total neoadjuvant chemotherapy (TNT) is now being performed to increase compliance with postoperative treatments and start systemic chemotherapy earlier for micrometastasis. The concept of TNT for LARC was initially examined in a clinical trial by Chau et al., who reported that induction or consolidation therapy achieved pCR in more than 20% patients receiving neoadjuvant capecitabine/oxaliplatin [7, 8]. Randomized control trials on TNT have recently been performed, in which induction or consolidation therapy or long- or short-course RT were selected [9–11]. The randomized RAPIDO trial, which used TNT consisting of short-course CRT and consolidation chemotherapy with the oxaliplatin regimen, reduced the probability of distant metastasis, but did not prolong overall survival (OS) or achieve better local control than long-course CRT [9]. The randomized PRODIGE 23 trial treated patients with neoadjuvant therapy that included FOLFIRINOX and a long-course CRT protocol, and reported longer disease-free survival (DFS); however, it did not stratify the OS curve compared to long-course CRT [10]. Based on the findings of these two trials, neoadjuvant systemic chemotherapy with the oxaliplatin regimen may reduce distant metastasis. Furthermore, a non-randomized phase II trial demonstrated that long-course CRT and two or four cycles of mFOLFOX-6 prolonged DFS [12]. Therefore, we selected long-course CRT followed by more than two cycles of the oxaliplatin regimen in the present trial on LARC patients at a high risk of distant metastasis and whose features included a suspected T4b tumor, lateral pelvic lymph node metastasis, or extramural venous invasion [9]. We also developed long-course CRT accompanied by oral 5-FU drugs with irinotecan (TEGAFIRI) in a clinical phase I/II study to increase the rate of pCR [13]. In this clinical trial, we aim to develop a new protocol that is consistent with the TEGAFIRI regimen for CRT and the oxaliplatin-based regimen for consolidation chemotherapy for LARC.

## Materials and methods

### Study design

The present study will be an open-label, single-arm, single-center prospective phase-II trial to establish the total neoadjuvant chemotherapy protocol. Preoperative CRT, followed by three cycles of mFOLFOX-6 chemotherapy or two cycles of CAPOX chemotherapy will be performed prior to TME (open, laparoscopic, or robotic). Nine cycles of mFOLFOX-6 chemotherapy or six cycles of CAPOX chemotherapy will then be administered postoperatively to patients with resectable locally advanced rectal adenocarcinoma at a high risk of distant metastasis, including the pretreatment status of a suspected T4b tumor, lateral pelvic lymph node metastasis, or extramural venous invasion. The treatment algorithm is shown in Fig. 1. Pretreatment CT and MRI will be used to diagnose all patients. The study protocol has been approved by the Ethics Committee of the University of Tokyo Hospital and the University of Tokyo Clinical Research Ethical Committee (approval No.: 2021508SP) and is registered in the Japan Registry of Clinical Trials (jRCT, approval No.: jRCTs031210660). This study was opened in March 2022. In modification protocol, including explanatory documents and consent forms, and various procedure manuals are to be changed, the principal investigator must consult with the University of Tokyo clinical research review committee prior to the change. After receiving the board’s review and approval, the change’s details will be reported to the hospital director. Then, submit a notification of changes to the implementation plan to the Minister of Health, Labor and Welfare by registering with jRCT.

**Fig. 1 Fig1:**
[figure not shown]
Flow diagram of the trial

### Sample size

The target sample size was set as 30 patients based on the confidence interval (CI) width. According to a previous clinical trial [9], we estimated the incidence of adverse events (AE) to be 40% in the present study protocol. The two-sided 95% CI ranged between 22.7 and 59.4% with the enrollment of 30 patients. A previous study showed that the incidence of AEs in the historical control was approximately 30% [13]; therefore, 30 patients fulfilled the desired precision because the incidence of AEs in the estimated upper 95% CI is not more than twice that in the control group.

### Study objectives

The primary outcome will be the incidence of AEs during total neoadjuvant therapy at the end of adjuvant FOLFOX or CAPOX therapy. AEs will be evaluated according to the National Cancer Institute Common Terminology Criteria for Adverse Events (CTCAE) version 5.0. Secondary objectives will be the evaluation of long-term outcomes, including distant relapse-free survival at 3 years, relapse-free survival at 3 years, the local recurrence rate at 3 years, and overall survival. Furthermore, pCR rates; postoperative morbidity and mortality rates; the dose intensity for each regimen, including CRT, neoadjuvant chemotherapy (NAC), and adjuvant therapy; and compliance with the study protocol, defined as completing full-dose treatment in each regimen, will be secondary endpoints.

### Patient selection

Thirty patients with locally advanced rectal adenocarcinoma will be enrolled. Patients will be 20–80 years old and meet inclusion and exclusion criteria (Table 1).

**Table 1 Tab1:** Inclusion and exclusion criteria

Inclusion Criteria			Exclusion Criteria	
1)	A tumor located below the peritoneal reflection or a rectal tumor reaching the peritoneal reflection		1)	Patients with a history of drug hypersensitivity
2)	Patients with histologically confirmed adenocarcinoma		2)	Patients for whom UFT/UZEL is contraindicated
3)	Patients judged to fall under any of the following by a preoperative diagnosis using MRI or CT		3)	Patients for whom the administration of CPT-11 is contraindicated
	(1) Infiltration into the surrounding organs (T4b, any N)		4)	Patients with UGT1A1*6/*6, UGT1A1*28/*28, and heterozygotes (UGT1A1*6/*28)
	(2) Suspected advanced lymph node metastasis, such as lateral lymph node metastasis		5)	Patients for whom the administration of 5-FU is contraindicated
	(3) Suspected extramural venous invasion		6)	Patients for whom the administration of LV is contraindicated
4)	Patients without distant organ metastasis		7)	Patients for whom the administration of L-OHP is contraindicated
5)	Patients aged between 20 and 80 years (at the time of obtaining consent)		8)	Patients for whom the administration of capecitabine is contraindicated
6)	Patients in whom radiation therapy, chemotherapy, or hormone therapy has not been performed as a pretreatment		9)	Patients receiving flucytosine, phenytoin, and potassium warfarin
7)	Patients who ingest food and may be orally administered drugs		10)	Patients with active infectious diseases (fever 38.0 °C or higher)
8)	Patients in whom the functions of the major organs are sufficiently maintained.		11)	Patients with serious complications
	The doctor will make a judgment based on the following values:		12)	Patients with diarrhea (more than 4 times a day or watery stools)
	a. White blood cell count: 4,000/mm^3^ and higher, and 12,000/mm^3^ and lower		13)	Patients with clinical brain metastases and those with a history of brain metastases
	b. Number of neutrophils: 2,000/mm^3^ or higher			Patients with simultaneous double cancer or metachronous double cancer with a disease-free period of 5 years or less
	c. Platelet count: 100,000/mm^3^ or higher		14)	Pregnant or lactating women or those with the desire to become pregnant
	d. Hemoglobin: 9.0 g/dl or higher		15)	Men who wish to have children
	e. Total bilirubin: 1.5 mg/dl or lower		16)	Other patients that the doctor in charge deems inappropriate as a target
	f. AST (GOT)/ALT (GPT): 100 IU/L and lower			
	g. Serum creatinine clearance using the Cockcroft-Gault estimation formula: 60.0 mL/min and more			
	* * If creatinine clearance by 24-hour urine collection is measured, that value is used.			
	If there is no measured value, calculate the estimated value using the Cockcroft-Gault estimation formula:			
	Male: creatinine clearance = body weight × (140-age) / (72 × serum creatinine level)			
	Female: creatinine clearance = 0.85 × {weight × (140-age) / (72 × serum creatinine level)}			
9)	Patients with no abnormal electrocardiogram findings (abnormalities without clinical issues are acceptable)			
10)	Patients with an Eastern Cooperative Oncology Group Performance Status of 0 to 1			
11)	Patients without sensory neuropathy			
12)	The research subject has given written consent to participate in the study			

### Data collection, monitoring, and auditing

Table 2 shows the schedule for the assessment. The principal investigator and sub-study investigator will monitor and assess the clinical course, safety, and efficacy outcomes recorded in medical records and complete the case report form (CRF). All CRF will be submitted to a separate department for data management, which will be appointed by the principal investigator, in the University of Tokyo. The monitor will perform verification based on “Written procedure for the study monitoring” during the study. Among CRFs, severe cases will be reported to the Ethical Committee within 30 days. No auditing is planned as part of this exploratory study.

**Table 2 Tab2:** Assessment schedule summary

	Pretreatment assessment	Chemoradiotherapy (CRT) UFT/UZEL+CPT-11 + RT	Post CRT	Consolidation chemotherapy (FOLFOX or CAPOX)	Post CTx
Informed consent•Case registration	●				
Obtaining medical history	●				
Subjective and objective findings	●	●	●	●	●
Laboratory tests	●	●	●	●	●
Imaging test	●		●		●
Confirmation of medication status		●		●	

### Data analysis

Patient baseline characteristics will be used to calculate summary statistics and distributions. The frequency and proportions of the categories for nominal variables are displayed for each group. Summary statistics (the number of cases, mean, standard deviation, minimum, median, and maximum) for continuous variables will be calculated for each group. The primary outcome analysis as an interval estimation of the incidence of AEs (CTCAE ≥ grade 3) is performed using an accurate CI based on the binomial distribution. The incidence of severe adverse events (AEs), the primary endpoint, might be higher in the TNT group than in patients who received preoperative chemoradiation with UFT/UZEL plus CPT-11 at our department (historical control group). If necessary, the ratio of severe AEs will be compared using Fisher’s exact calculus test.

### Treatment plan

Patients who meet the eligibility criteria will be informed of all details about the study procedure. They will receive CRT, mFOLFOX-6, or CAPOX; undergo radical surgery at approximately week 21; and receive another course of mFOLFOX-6 or CAPOX (Fig. 1). Only patients who voluntarily participate in the study and provide informed consent will be enrolled.

### Preoperative CRT

CRT will be performed as previously described [13]. Briefly, CRT consists of long-course radiation (50.4 Gy/28 fractions, five days per week) on days 1–38, concurrent with oral and intravenous chemotherapy (TEGAFIRI; tegafur/uracil, oral leucovorin, irinotecan). During RT, UFT (300 mg/m^2^/day for less than 1.17 m [2], 400 mg/m^2^/day from 1.17 to 1.49 m [2], 500 mg/m^2^/day from 1.50 to 1.83 m [2], and 600 mg/m^2^/day for more than 1.83 m [2]) and LV 75 (mg/day) will be orally administered on the days of RT, while irinotecan (80 mg/m^2^) will be intravenously administered on days 1, 15, 29, and 43.

A physical examination, laboratory test, and AE assessment will be performed at every irinotecan injection. AEs that occur during or after the cycle administration will be collected.

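### The UFT dose is set by body-surface-area band but printed in mg/m²/day, so area counts twice; the bands fit flat daily doses in mg

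*Protocol article*

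**What the plan says.** The Preoperative CRT section of the protocol article gives four UFT doses, each tied to a range of body surface area. The two lower bands read "300 mg/m^2^/day for less than 1.17 m [2], 400 mg/m^2^/day from 1.17 to 1.49 m [2" and the two upper bands "500 mg/m^2^/day from 1.50 to 1.83 m [2], and 600 mg/m^2^/day for more than 1.83 m [2". The same sentence gives the other two drugs. For leucovorin it says "LV 75 (mg/day) will be orally administered on the days of RT". The entry for the intravenous drug is "irinotecan (80 mg/m^2^) will be intravenously administered on days 1, 15, 29, and 43". The section opens with a reference to an earlier report of the regimen: "CRT will be performed as previously described".

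Two secondary endpoints in Study objectives depend on a planned dose. The first is "the dose intensity for each regimen, including CRT, neoadjuvant chemotherapy (NAC), and adjuvant therapy". The second, which measures adherence, is "compliance with the study protocol, defined as completing full-dose treatment in each regimen".

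**The concern.** A dose is normally scaled to body size in one of two ways: one figure per square metre multiplied by the patient's area, or a flat daily amount read from a table of area bands. The UFT line does both. The dose per square metre then rises from 300 to 600 as patients get larger, and the article gives no reason for that. The other drugs in the sentence each follow one convention: irinotecan is a single per-m² figure without bands, and leucovorin is a flat daily dose.

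This is the only place where the article states the UFT dose. The trial's primary outcome is the incidence of adverse events, and its aim is a new treatment protocol that others may copy. A reader who applied the line literally would overdose UFT. If the same unit were carried into the analysis, the reference dose for dose intensity and full-dose completion would also be wrong.

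The broken superscript in the band limits, where the square of the metre became a citation mark, is a text-conversion artefact and no part of the point. The per-m² unit is intact on all four doses.

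**Working it through.** **Inputs** (Protocol article, Preoperative CRT): doses 300, 400, 500 and 600, printed in mg/m²/day; bands below 1.17, 1.17 to 1.49, 1.50 to 1.83, and above 1.83 m².

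**1. The printed unit taken literally.** Daily amount = dose × area. The excess over a flat dose is (area − 1).

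| Area (m²) | Literal (mg/day) | Flat (mg/day) | Excess |
|---|---|---|---|
| 1.17 | 400 × 1.17 = 468 | 400 | 17% |
| 1.49 | 400 × 1.49 = 596 | 400 | 49% |
| 1.50 | 500 × 1.50 = 750 | 500 | 50% |
| 1.83 | 500 × 1.83 = 915 | 500 | 83% |
| 1.84 | 600 × 1.84 = 1104 | 600 | 84% |

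The daily amount would jump from 596 to 750 mg between 1.49 and 1.50 m², and from 915 to 1104 mg between 1.83 and 1.84 m².

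**2. The figures taken as flat mg/day.** Dose per m² = dose / area.

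- 300/1.00 = 300.0 and 300/1.16 = 258.6
- 400/1.17 = 341.9 and 400/1.49 = 268.5
- 500/1.50 = 333.3 and 500/1.83 = 273.2
- 600/1.84 = 326.1 and 600/2.00 = 300.0

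Over assumed areas of 1.00 to 2.00 m² the dose stays between 259 and 342 mg/m²/day. Near the middle of the two closed bands it is 400/1.33 = 300.8 and 500/1.665 = 300.3.

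**3. Where the band limits come from.** If a constant target of D mg/m²/day is rounded to the nearest 100 mg, the rounded dose changes at 350/D, 450/D and 550/D.

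| Target D | 350/D | 450/D | 550/D |
|---|---|---|---|
| 275 | 1.273 | 1.636 | 2.000 |
| **300** | **1.167** | **1.500** | **1.833** |
| 325 | 1.077 | 1.385 | 1.692 |
| Printed limits | 1.17 | 1.50 | 1.83 |

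Only 300 mg/m²/day fits of the three. At the band edges, 300 × area gives 348, 351, 447, 450, 549 and 552 mg at 1.16, 1.17, 1.49, 1.50, 1.83 and 1.84 m². These round to 300, 400, 400, 500, 500 and 600, as printed. The value at 1.50 m² is an exact tie and must be rounded up. With that convention, all 111 areas from 1.00 to 2.10 m² in steps of 0.01 agree with the printed band figure.

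**4. What a wrong reference dose would do.** A patient of 1.60 m² taking 500 mg/day would be measured against 500 × 1.60 = 800 mg/day if the printed unit were used. That gives 500/800 = 62.5% relative dose intensity and a failure on full-dose completion, for a patient who took every planned dose.

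**5. What is untouched.** The Sample size section states "The two-sided 95% CI ranged between 22.7 and 59.4% with the enrollment of 30 patients". The exact binomial interval for 12 of 30 is 22.66% to 59.40%, so that figure reproduces and uses no dose.

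**The case against.** The strongest case on the other side is that nothing in the trial is shown to go wrong. The paragraph is a short summary that points to a published regimen, the same group developed that regimen, and the trial runs at one center. The dose-reduction tables are in a supplement that is not shown. An overdose would need an outside reader to prescribe from a condensed article without opening the reference. The link to dose intensity and compliance also depends on the full protocol carrying the same unit. Finally, the 300 mg/m²/day target is inferred, since the article never states it.

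Most of this stands, and it limits the point. This is a wrong unit in a document, with no evidence of wrong treatment, and the excess doses above measure the gap between two readings of a sentence. The endpoint consequence is conditional. The replacement text should be confirmed at source before it is printed. None of this makes the line correct as written. The reference does not alter the printed unit, no other section of the article corrects it, and three limits that match to two decimals are strong evidence for mg/day.

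**Conclusion.** The concern holds. The UFT doses are printed in the wrong unit, and the article's own band limits indicate flat doses of 300, 400, 500 and 600 mg/day. The literal reading exceeds the flat reading by 17% to 49% in the 1.17 to 1.49 m² band, by 50% to 83% in the 1.50 to 1.83 m² band, and by 84% at 1.84 m².

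The conclusion rests on an inferred target of 300 mg/m²/day, on rounding to 100 mg steps with ties upward, and on assumed areas of about 1.00 to 2.10 m². It is most likely an error confined to the article. It deserves correction because it concerns the dose of a cytotoxic drug in a safety trial and is the only UFT dose that the article gives.

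**What to change.** Check the sentence against the approved protocol and the cited report of the CRT regimen. If they confirm flat dosing, as the band limits indicate, print: UFT 300 mg/day (below 1.17 m²), 400 mg/day (1.17 to 1.49 m²), 500 mg/day (1.50 to 1.83 m²) and 600 mg/day (above 1.83 m²). Use these as the planned doses for UFT dose intensity and full-dose compliance. If the approved protocol or the supplementary dose tables carry the per-m² unit, correct them as well.

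The cost is a document check and a one-line correction. Sample size, endpoints and the primary analysis do not change.

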### Neoadjuvant systemic chemotherapy

Four to eight weeks after the completion of RT, patients will receive NAC, including three cycles of mFOLFOX-6 or two cycles of CAPOX. The mFOLFOX-6 regimen consists of the following: oxaliplatin 85 mg/m^2^ intravenously administered and 5-FU 400 mg/m^2^ administered as an intravenous bolus on day 1, followed by 2400 mg/m^2^ intravenously administered over 24 h on days 1–2, and leucovorin 200 mg/m^2^ intravenously administered on day 1. One cycle of mFOLFOX-6 is 14 days. The CAPOX regimen consists of the following: oxaliplatin 130 mg/m^2^ intravenously administered on day 1 and capecitabine 2000 mg/m^2^ orally administered twice a day on days 1–14 in every cycle. One cycle of CAPOX is 21 days. A physical examination, laboratory test, and AE assessment will be performed at the time of every oxaliplatin injection. AEs that occur during or after the cycle administration will be collected.

### Rectal resection

Radical surgery will be performed 4 to 8 weeks after the completion of NAC. Lateral lymph node dissection will be selectively performed on patients with suspected lateral lymph node metastasis before CRT. All resected specimens will be pathologically analyzed according to the American Joint Committee on Cancer classification [14]. The pathological therapeutic response of the primary tumors will be assessed according to the Japanese Classification of Colorectal, Appendiceal, and Anal Carcinoma of the Japanese Society for Cancer of the Colon and Rectum [15]. The frequency and grade of surgical complications within 30 days of surgery will be evaluated using the Clavien-Dindo classification.

### Adjuvant systemic chemotherapy

Patients will receive adjuvant chemotherapy within 12 weeks of surgery, including nine cycles of mFOLFOX-6 or six cycles of CAPOX. AEs that occur during or after each cycle administration will be collected. A physical examination, laboratory test, and AE assessment will be performed at the time of every oxaliplatin injection. If patients cannot start to receive adjuvant chemotherapy or if adjuvant chemotherapy is discontinued prematurely, the follow-up period will be started in these patients.

#### Chemotherapy administration criteria and dose reduction criteria

Chemotherapy administration criteria are shown in Supplementary Table 1. The criteria consist of number of hematologic toxicities, including white blood cells, neutrophil, platelets, and non-hematologic toxicities, including nausea and hand-foot syndrome. Chemotherapy is interrupted until the criteria are met. The dose reduction criteria and the reduced doses are shown in Supplementary Tables 2 and Supplementary Tables 3, respectively. Each chemotherapeutic drugs should be reduced when hematologic and non-hematologic toxicity ≥ Grade 3 is observed. In addition, doses can be reduced at the physician’s discretion to ensure safety.

